## Abstract

**Background::**

Atrial fibrillation (AF) is the most common sustained arrhythmia worldwide. Oral anticoagulation is an effective strategy for primary and secondary prevention of stroke in patients with AF. Warfarin is an oral anticoagulant widely prescribed and, despite its benefits, the achievement of the goals of drug therapy depends on patient involvement, among other factors. Educational interventions can contribute for effectiveness and safety of oral anticoagulation therapy. We sought to describe the protocol of a clinical trial designed to evaluate the effect of a patient-centered educational strategy focused on low-income patients with AF and poor anticoagulation control.

**Methods::**

Patients ≥18 years with AF, on warfarin for at least 6 months and time in therapeutic range (TTR) <60% will be recruited at 2 anticoagulation clinics (ACs) in Brazil. Patients from 1 AC will be allocated to the intervention group and patients from the other AC will be allocated to the control group. Intervention group will attend educational sessions based on a patient-centered care approach, and the control group will receive usual care. The intervention will be based on Paulo Freire's theory and tailored according to practices involving health empowerment and techniques applied to individuals with limited socioeconomic status. The intervention is estimated to last 5 months. We will consider TTR as the primary outcome and knowledge and self-reported non-adherence to warfarin therapy as secondary outcomes. TTR values and non-adherence will be measured before intervention (T0) and at times immediately after (T1), and 3 (T2), 6 (T3), 9 (T4), and 12 (T5) months after intervention. Knowledge will be measured at times T0, T1 e T5. The calculated sample size indicated 85 patients in each group.

**Discussion::**

The proposed study aims to investigate whether an innovative educational approach to deliver care to a low-income population on warfarin improves anticoagulation control. Once our hypothesis is confirmed, our findings are expected to help improving anticoagulation control, knowledge on warfarin therapy and adherence to drug therapy. Thus, we believe our results may contribute to improve oral anticoagulation effectiveness in a low-income population.

Trial registration: Registro Brasileiro de Ensaios Clínicos (ReBEC) RBR- 9cy6py and UTN: U1111-1217-0151 (March, 2019).

## Introduction

1

Atrial fibrillation (AF) is the most common sustained arrhythmia worldwide.^[1]^ It is considered a public health challenge, with high comorbidity, increased mortality risk and high incremental health cost.^[1,2]^ It is as an independent factor for stroke,^[1]^ and oral anticoagulation is an effective strategy on primary and secondary prevention of cardioembolic stroke on patients with AF.^[3,4]^ Despite the availability of the direct oral anticoagulants, warfarin is still widely used in this context.^[5]^

Warfarin exhibits a narrow therapeutic index, a wide variability of dose-response and the potential to interact with many drugs and foods containing vitamin K. Adjustments on warfarin dosages are guided by regular monitoring of prothrombin activity, expressed by the International Normalized Ratio (INR). Oral anticoagulation control is challenging due to several aspects, such as INR oscillations, the need of frequent dose adjustments, influence of genetic polymorphisms, non-adherence to drug therapy, among others.^[4]^ Poor anticoagulation control increases the risk of hemorrhagic and cardioembolic events.^[6,7]^

Anticoagulation quality is often measured by the time in therapeutic range (TTR) which is a method useful to identify the proportion of time patients attain INR values within the desired therapeutic target.^[8]^ Low values of TTR are influenced by sociodemographic factors, such as low family income and inadequate health literacy.^[9]^ Average TTR below 60% is associated with higher incidence of hemorrhagic and cardioembolic events.^[6,7]^ Therefore, the assessment of anticoagulation control may help to stratify patients with higher risk of complications. These patients could benefit from patient-centered educational strategies designed to improve their active participation in self-care and drug adherence.

A systematic review performed by Clarkesmith et al^[10]^ pointed out the existence of evidence gaps related to the impact assessment of educational strategies focused on patients taking oral anticoagulants. All studies included in the review were performed in high-income countries and the studies usually exclude patients with inadequate health literacy^[10]^ which would benefit the most from educational interventions.^[9]^ In the context of low- and middle-income countries, some findings have reinforced the need of investments on strategies to improve knowledge on oral anticoagulation.^[11,12]^ In those countries, there are significant barriers that hinder the health education process in vulnerable populations. As an alternative, educational strategies using the principle of empowerment may contribute to encourage patients in self-care and potentially would improve the results of drug therapy. Although there is evidence of impact from patient-centered educational strategies for chronic disease management,^[13,14]^ the evidence is lacking for patients taking warfarin. Thus, we aimed to describe the protocol of a controlled clinical trial designed to evaluate the effect of a patient-centered educational strategy focused on low-income patients with AF and poor anticoagulation control.

## Methods

2

### Study setting

2.1

This is a non-randomized controlled clinical trial to be conducted at 2 public university hospitals in Belo Horizonte, a 3.5-million-inhabitant city in Southeast Brazil. Patients will be recruited at 2 anticoagulation clinics (ACs) from the hospitals Hospital das Clínicas da UFMG (HC-UFMG) and Hospital Risoleta Tolentino Neves (HRTN). Patients from the former AC will be allocated to the intervention group and patients from the latter AC will be allocated to the control group.

These study settings are tertiary referral hospitals. More than 90% of patients perform INR at the hospital laboratory. Those ACs are multidisciplinary with a team composed by physicians, pharmacists, and nurses. Specialized care is regularly provided to outpatients who receive education and warfarin dose adjustments. Both ACs have similar anticoagulation protocols to guide professionals to perform standardized care practice. The trial has been registered on Registro Brasileiro de Ensaios Clínicos (REBEC) (http://www.ensaiosclínicos.gov.br). We followed the SPIRIT recommendations to describe the study protocol.^[15]^

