### Sample size

2.5

Sample size was calculated using diggle.linear.power function of longpower package in the software R 3.4.4 version.^[21]^ The TTR will be prospectively assessed, from T0 to T5. We considered an absolute increase of 6% in TTR with standard deviation of 7.5,^[22]^ 80% power, level of significance of 0.05 and at least 15% of variation in the slope coefficient between intervention and control groups. The calculated sample was 71 individuals for each group, and we planned to include 20% additional patients to account for a follow-up loss, resulting in 85 individuals allocated in each group. Also, we used composite symmetry autocorrelation structure with a correlation of 0.80 between the times of data collection.

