### Recruitment

2.6

Before recruitment, all patients assisted between August 2017 and September 2017 at the studied ACs (n = 1371) had their TTR calculated to identify those presenting TTR <60%. A new TTR calculation occurred between July and December 2018 to certify if patients with low TTR (<60%) identified in the first screening would continue to fulfill inclusion criteria. Thus, patients with persistently low TTR will be invited to participate in the study. To complete the sample, new patients with low TTR between July and December 2018 will be considered for inclusion in the study. Recruitment phase started in January and is expected to end by May. Patients’ invitation is planned to take place before or after scheduled appointments for monitoring oral anticoagulation.

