As limitations, we should address that the studied patients will be randomized intragroup, but not intergroup. Moreover, we will not identify definitive outcomes, such as hemorrhagic and thromboembolic complications. This derives from the limitation of data collection regarding the history of previous of INR values and occurrence of adverse events. Patients who presented adverse events may have been admitted by other healthcare institutions hindering the access to patient clinical history.

Our study will allow testing the intervention in a real-world, in a country that has a significant proportion of patients with limited socioeconomic status, who do not have wide access to alternative anticoagulation therapies instead of warfarin. The perspectives of our findings include the potential to contribute for future strategies involving patients on warfarin assisted by the Brazilian Unified Health System (Sistema Único de Saúde—SUS). Besides, we believe that our findings can contribute to improve health education actions directed to low-income patients with AF treated with warfarin in other countries in the world.

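### With one clinic per arm, the stated 80% power and 0.05 level hold only if the two clinics' TTR trends would otherwise be parallel, and the protocol does not state that condition

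*Protocol article*

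**What the plan says.** Section 2.1 (Study setting) describes the design openly: "This is a non-randomized controlled clinical trial to be conducted at 2 public university hospitals". Allocation is by clinic: "Patients from the former AC will be allocated to the intervention group", and the other clinic's patients form the control group.

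Section 2.5 (Sample size) uses a patient-level slope formula. The inputs are "We considered an absolute increase of 6% in TTR with standard deviation of 7.5" and "80% power, level of significance of 0.05 and at least 15% of variation in the slope coefficient between intervention and control groups". The only dependence term is a compound-symmetry correlation of 0.80 between one patient's repeated measurements. The result is 71 per group, raised to 85 for losses.

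Section 2.9 (Statistical analysis) fits GEE models to patients. Variables are screened at 0.20 and then at 0.05, and the final model keeps only significant coefficients.

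Section 2.4 (Outcomes) plans comparisons within and between groups from T0 to T5, with T0 the only outcome point before the intervention.

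The Discussion gives avoidance of contamination as the reason for separate centres, and cites similar management protocols as a strength. Among the limitations it says that "the studied patients will be randomized intragroup, but not intergroup".

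**The concern.** With two clinics and two arms there are no between-clinic degrees of freedom. No covariate and no standard error computed from patients can separate an effect of the education from a change that happened at one clinic and not the other. Staffing, dosing practice or case mix may shift differently over the study.

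Selection adds a route to this. Patients enter because TTR was below 60%, and section 2.6 mixes persistently low patients with newly low ones to complete the sample. If that mix differs by clinic, so may regression to the mean. A single T0 can correct for a difference in level but cannot show a difference in trend.

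At stake is what a significant result means. Without the condition of parallel trends, the p-value tests a difference between two clinics, not the effect of the education.

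**Working it through.** **Inputs from section 2.5.** SD 7.5 (variance 56.25), within-patient correlation 0.80, six measurements, 71 per group, 80% power, alpha 0.05. Sidedness is not stated; two-sided is assumed.

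**The plan's own figure.** The slope formula is n per group = 2(1.96 + 0.84)² × 56.25 × (1 − 0.80) / (Sxx × d²). Here d is the slope difference and Sxx is the sum of squared deviations of the visit times. The protocol states neither the time coding nor the base of the 15%, so 71 does not follow unambiguously:
- A 6-point difference over T0–T5 needs about 7 per group (visits coded 0–5).
- A difference of 15% of 6, or 0.9 points, needs about 311 per group (same coding).
- A slope difference of 0.15 per month with visits at months 0, 1, 3, 6, 9 and 12 gives 70.8, i.e. 71. This is a back-fit, not a stated input. It implies 0.15 × 12 = 1.8 points, and it does not match a 5-month intervention followed by 12 months.

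Three codings are therefore carried forward.

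**Patient-level SE at 71 per group.** SE of the difference in change, first to last visit = span × √(2 × 56.25 × 0.20 / (Sxx × 71)). The difference detectable with 80% power is 2.80 × SE.

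| Time coding | Span | Sxx | SE (points) | Detectable (points) |
|---|---|---|---|---|
| Months 0, 1, 3, 6, 9, 12 | 12 | 110.83 | 0.642 | 1.80 |
| Visits 0–5 | 5 | 17.5 | 0.673 | 1.89 |
| Months 0, 5, 8, 11, 14, 17 | 17 | 190.83 | 0.693 | 1.94 |

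**Fixed differential drift b, no intervention effect.** Rejection rate = Φ(b/SE − 1.96) + Φ(−b/SE − 1.96).
- b = 0: 5%.
- b = 0.5: 11–12%.
- b = 1: 34%, 32% and 30% for the three codings in table order.
- b equal to the detectable difference: 80%, the same as for a real effect of that size.
- At 85 per group, b = 1 gives 40%, 37% and 35%. Extra patients narrow the SE around the same bias.

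**Random clinic drift with SD τ per clinic (assumed).** Total SE = √(SE² + 2τ²). Type I error = 2(1 − Φ(1.96 × SE / total SE)). Power, if the test used the total SE, = Φ(effect / total SE − 1.96). For SE 0.642 the total SE is 0.733, 0.955 and 1.553.

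| τ (points) | Type I error | Power, detectable effect | Power, 6 points |
|---|---|---|---|
| 0.25 | 8–9% | 69–70% | >99% |
| 0.5 | 17–19% | 47–50% | >99% |
| 1.0 | 39–42% | 21–23% | about 97% |

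Ranges run over the three codings.

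**Sensitivity to the SD.** If the SD were 15 rather than 7.5 (assumed), a fixed drift of 1 point would give 11.5% false positives and 2 points 31.8% (visit coding).

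**The case against.** The strongest reply is that the design is disclosed and reasoned. The protocol calls itself non-randomised, explains why the groups are in separate centres, and lists the lack of randomisation between groups as a limitation. Details of a trend sensitivity analysis can also properly sit in an analysis plan that is not shown. All of that stands, and nothing is concealed. But neither the Study setting nor the limitations attaches the condition to the power and significance level in section 2.5.

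The reply also rules out four stronger readings that a reader might draw:
- *Every clinic difference goes into the effect.* It does not. Outcomes are compared before and after, and the sample size rests on a slope difference, so constant differences cancel. Only differential change over time remains.
- *A small drift is indistinguishable from the planned effect.* That depends on the effect meant. It is fair for the 1.8–1.9 points that 71 per group can detect. A drift of 1 point does not equal the 6 points that section 2.5 states, and power for 6 points stays at about 97% or more in the table.
- *The stated power is simply false.* It is conditional. The documents give no clinic-level figure, so the drift sizes are assumptions, and τ cannot be estimated with one clinic per arm.
- *Existing screening data give each clinic's trend, which can be subtracted.* For 2017, "all patients assisted between August 2017 and September 2017 at the studied ACs (n = 1371) had their TTR calculated". The July–December 2018 calculation is described as a recheck of patients already found low and a search for newly low ones. Setting all patients against a set selected on low TTR would mix trend with regression to the mean, and subtracting the result could add bias.

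**Conclusion.** The point holds in a limited form. Clinic and arm coincide, so the 80% power and 0.05 level hold only under parallel clinic TTR trends, a condition the protocol does not state. Parallel trends are necessary for the stated figures but not sufficient, since 71 itself depends on an unstated reading of the inputs.

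On the protocol's SD and correlation, an assumed 1-point differential drift raises the false-positive rate to about 30–34%. Assumed drift SDs of 0.25, 0.5 and 1.0 raise it to about 8–9%, 17–19% and 39–42%. These are illustrations, and a larger SD would soften them.

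The limitation about randomisation within groups is a separate wording fault. Section 2.1 says the trial is non-randomised, and section 2.6 describes screening and invitation with no random step. A reader might infer that the sentence claims protection against bias, but it stands among the limitations and supports no more than an inconsistency.

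**What to change.** - **Section 2.5 and the limitations:** state that power and p-values assume no clinic-by-time difference. Commit to a sensitivity or tipping-point analysis giving the differential drift that would overturn the result, with drift sizes labelled as assumptions.
- **Section 2.9:** name the group × time contrast (change from T0) as the primary effect, and keep it in the model whatever the p-value screening shows. Compare pre-intervention TTR between clinics only in the same defined patient set at both dates, and only descriptively. Do not subtract a trend built from the all-patient 2017 set and the low-TTR 2018 set.
- **Discussion:** reconcile the statement on randomisation within groups with the non-randomised design in section 2.1, and limit the conclusion to a comparison of two clinics.

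The cost is some wording, a little more analysis and a less favourable power statement. No extra patients are needed, and extra patients at these two clinics would not help. Estimating clinic variation would take more clinics per arm, which is a different trial.

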### Eligibility criteria

2.2

Patients assisted at the 2 ACs will be considered as potentially eligible for study participation. The inclusion criteria will be age ≥18 years, both sexes, follow-up in the ACs for at least 6 months, valvular or non-valvular AF as indication for warfarin use and TTR<60%. The exclusion criteria will be bedridden patients or limitation of locomotive disorders that compromises the attendance to office visits; total blindness or deafness; aphasia or other speech disorders that could hinder communication during study; dementia diagnosis reported in medical records; less than 2 INR values in the study period. Relatives or caregivers will be allowed to participate in the intervention, but they will not be assessed in this study. Follow-up loss will be considered as the absence in at least 2 intervention appointments or 2 or more intervention replacements.

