**Figure 1 F1:**
[figure not shown]
Intervention plan. AF = atrial fibrillation, TTR = time in therapeutic range.

The topics selected for the intervention sessions were: “knowing the medical condition and the anticoagulation indication”, “appropriate use of warfarin and other drugs taken by the patient”, “drug-drug and drug-food interaction?” and “risks and benefits from the treatment”.^[8,20]^

The intervention will be developed in groups of 12 participants at maximum. It will begin with a “culture circle”, defined as a learning method based on “generating words” that reflect the participants’ life experiences. The “generating words” will be identified by an immersion of the researcher in patient care process. Recognition of the context and the patients’ needs about the care process will be carried out. The educator will promote a debate to strongly motivate each group participant. Patients will be encouraged to share their life experiences and fears with other people who may have similar experiences. Thus, they will be able to develop a critical opinion out of their own background.^[16,17]^

Each group of 12 patients will participate in 4 face-to-face meetings, with intervals of approximately 30 days. As the topics will be repeated in each group, patients who miss a meeting will have other opportunities to attend the missing topic. Each meeting will be composed by a warm-up step, followed by the topic presentation and the learning construction. Participants will be invited to exchange experiences about warfarin therapy, to identify their main goals and obstacles, and to set future goals to be pursued. Each meeting is planned to last 1 hour, with a possible extension to 1 hour and a half, when necessary.

One clinical pharmacist trained on health education will conduct the intervention together with supervised Pharmacy undergraduates. Researchers will receive specific training by a senior researcher with experience in the methodology to develop skills in techniques to promote self-care and to stimulate patient empowerment. Pilot educational sessions will be offered to an independent group of patients with similar sociodemographic characteristics and a thrombosis history who are assisted at different week days of the intervention group at HC-UFMG. These patients will not be included in the study analyses. Researchers will not get involved in patient care during the study period, which will be under the responsibility of the AC professionals.

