### Statistical analysis

2.9

TTR will be calculated by the Rosendaal method using a linear interpolation of INR results. TTR will be calculated at least 2 INR measurements. For participants who had INR intervals higher than 56 days, we used INR values to calculate TTR for the valid intervals (<56 days) and afterward we used the independent TTR values to calculate the final TTR by the arithmetic mean.^[33]^

Categorical variables will be expressed as frequency and percentage. Symmetric continuous variables will be expressed as means and standard deviation while asymmetric data will be expressed as median, first quartile, and third quartile.

To evaluate significance of each variable in the outcomes, univariate models will be adjusted using generalized estimation equation (GEE) with appropriate distribution for each outcome (normal or gamma distribution for TTR and binomial distribution for knowledge and adherence). Wald tests will be performed for each variable coefficient using an initial significance level of 0.20. All variables identified as initially significant will be added to a multivariate model and significance level will be set at 0.05. One final GEE multivariate model will be presented for each outcome including exclusively significant coefficients. Post hoc analysis will include comparisons of outcome means (or probabilities) at different time points. Statistical analysis will be performed in R version 3.4.4.

Patient refusal, death or other situations that would make it difficult for the patient to continue in the study will be registered and they will be considered as an intention to treat for analysis. Important protocol modifications will be reported to REBEC.

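### Loss to follow-up is defined by attendance at educational sessions, so only the intervention arm can meet it, and this conflicts with the intention-to-treat statement

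*Protocol article*

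**What the plan says.** Section 2.2 (Eligibility criteria) of the protocol article ends with the only definition of loss: "Follow-up loss will be considered as the absence in at least 2 intervention appointments or 2 or more intervention replacements".

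The sessions belong to one arm. The abstract states: "Intervention group will attend educational sessions based on a patient-centered care approach, and the control group will receive usual care". Section 2.3 (Intervention) fixes their number: "Each group of 12 patients will participate in 4 face-to-face meetings, with intervals of approximately 30 days". It also offers make-up sessions: "patients who miss a meeting will have other opportunities to attend the missing topic". No definition of loss is given for control patients.

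Two other sections bear on what happens to a patient labelled as lost:

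- Section 2.5 (Sample size): "The calculated sample was 71 individuals for each group, and we planned to include 20% additional patients to account for a follow-up loss", which gives 85 per group.
- Section 2.9 (Statistical analysis) covers patients who refuse, die or otherwise cannot easily continue. It says that these events are registered and "they will be considered as an intention to treat for analysis".

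The exclusion criteria in 2.2 also list "less than 2 INR values in the study period", without saying which period is meant.

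**The concern.** Loss to follow-up should mean that the outcome could not be obtained. Here it means that the patient did not take up the intervention. Because only one arm has an intervention to take up, the rule can remove patients from that arm and never from the other.

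Patients who skip educational sessions are plausibly those who also skip warfarin doses, and adherence is itself a secondary outcome. If they are dropped or no longer measured, a set of attenders is compared with an unselected control group. The comparison has little protection to spare, since allocation is by clinic: "This is a non-randomized controlled clinical trial to be conducted at 2 public university hospitals in Belo Horizonte". The discussion also presents the study of a real-world rather than a highly selected population as a feature of the trial, and selection by attendance would work against that.

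The protocol does not settle whether such patients stay in. Sections 2.5 and 2.9 point in opposite directions, so the choice could be made after attendance is known.

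**Working it through.** **1. Who can meet the rule.** It counts absences from intervention appointments or replacements. Intervention patients have 4 meetings; control patients have none. The share of controls who can be lost under the rule is therefore 0% by construction.

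**2. Whether the outcome is missing when the rule is met.** Section 2.1 says that more than 90% of patients have INR done at the hospital laboratory. Section 2.3 leaves patient care with the clinic professionals. Section 2.7 takes adherence from hospital records. TTR and adherence can therefore still be obtained for most patients who miss two sessions. Knowledge is different: the test has to be given to the patient.

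**3. The plan's own figure.** 71 × 1.20 = 85.2, stated as 85, so the allowance reproduces. It leaves 85 − 71 = 14 patients per group who may be lost while the required 71 remain. The calculation thus treats lost patients as outside the analysed number. The base of 71 is taken as given. It cannot be reproduced uniquely, because the slope difference and time coding are not fully stated, and nothing below depends on it.

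**4. How many could meet the rule (assumption).** Suppose each meeting is missed independently with probability p. Then P(at least 2 of 4 missed) = 1 − (1 − p)^4 − 4p(1 − p)^3:

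- p = 10%: 1 − 0.6561 − 0.2916 = 5.2%
- p = 20%: 1 − 0.4096 − 0.4096 = 18.1%
- p = 30%: 1 − 0.2401 − 0.4116 = 34.8%

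**5. Shift in mean TTR if these patients are dropped (assumption).** Let there be no true effect. A share f of the intervention arm is dropped, and their mean TTR is g points below that of the patients kept. The kept mean then exceeds the full-arm mean by f × g. The second figure in each cell is the two-sided rejection probability at 0.05 for a single comparison of means, using the SD of 7.5 from section 2.5 and standard error 7.5 × √(1/n₁ + 1/85), where n₁ is the number kept.

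| f (n₁) | g = 2 | g = 5 | g = 7.5 | g = 10 |
|---|---|---|---|---|
| 10% (76) | 0.2; 5.3% | 0.5; 7.1% | 0.75; 9.7% | 1.0; 13.5% |
| 20% (68) | 0.4; 6.2% | 1.0; 13.0% | 1.5; 23.3% | 2.0; 37.4% |
| 30% (59) | 0.6; 7.6% | 1.5; 21.9% | 2.25; 42.5% | 3.0; 65.6% |

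The planned effect in section 2.5 is an absolute increase of 6%, that is, 6 TTR points.

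**6. What this means for change over time.** The table concerns mean level at one time point. If dropped patients are removed at T0 as well and the gap is constant, the shift is f × g both before and after, and the change from T0 is biased by f × g − f × g = 0. Bias in change then needs a different course over time in those removed. If they are kept at T0 and absent later, the observed means do not cancel. GEE does not reliably repair this, because dropout tied to attendance is unlikely to be completely at random. The between-group comparisons at single time points (sections 2.4 and 2.9) carry the shift in either case.

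**The case against.** The strongest reply is that no sentence says patients labelled lost are removed. Section 2.2 only attaches a label. The one sentence on handling is in 2.9, and it keeps patients who discontinue in the analysis. Read that way, the two sections could coexist. The 20% allowance is indirect evidence, and it is applied to both arms although the definition can be met in only one. This stands in part: removal is implied, not stated. But 2.9 does not say whether non-attendance is among its situations, and enlarging the sample for loss has no purpose if lost patients are analysed. If 2.9 does govern, the definition in 2.2 has no analytic role and misleads.

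Three stronger readings are tempting, and the text does not support them:

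- A reader might infer that patients who made up two sessions, and so received all four topics, are counted as lost. The phrase can mean using two replacements or being absent from two. Either way the rule is based on attendance and confined to one arm.
- A reader might infer that the exclusion for fewer than two INR values is decided on data arising after allocation. The period is undefined and could be the July to December 2018 screening window. The criterion applies to both arms and matches the minimum for computing TTR.
- A reader might infer that the rule alone could produce the hoped-for TTR gain. The largest shift in the table is 3.0 points, half of the planned 6. It needs a gap of 10 points, which is 1.33 times the planning SD (10/7.5), and it disappears from change scores under a constant gap with T0 removed. A slope difference worked back from 71 is no substitute benchmark: it is a different quantity from a level shift and cannot be recovered uniquely.

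**Conclusion.** The point holds as a defect in the rule as written. Loss to follow-up is defined by attendance, can occur in one arm only, and is not linked to missing outcomes. Section 2.5 implies that lost patients leave the analysis and section 2.9 says that patients who discontinue do not; these must be reconciled.

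Bias is conditional. It arises only if non-attenders are dropped or no longer measured. Its probable direction, towards the intervention, rests on the assumption that non-attenders have poorer TTR and adherence. Its size cannot be derived from the documents. The 0.2 to 3.0 points are an illustration in mean level, for 10% to 30% dropped and a gap of 2 to 10 points. The rejection probabilities belong to a simple comparison of means, not to the planned GEE.

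The correction is still needed before analysis, because it decides who enters the primary comparison.

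**What to change.** Replace the sentence in 2.2 with a rule of this kind: *A patient is lost to follow-up for an outcome at a time point if that outcome could not be obtained (no computable TTR, no adherence record, no knowledge test), by the same rule in both groups. Session attendance, including use of replacement sessions, is recorded as adherence to the intervention and does not affect inclusion in the analysis.*

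Then:

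- State in 2.9 that every enrolled patient with available outcome data is analysed in the arm of their clinic, whatever their attendance, and that any attendance-based analysis is secondary.
- State in 2.2 that the exclusion for fewer than two INR values refers to the pre-intervention window.

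The planned 85 per group is unchanged. The cost is a short amendment, reported to the registry as 2.9 already foresees for important modifications. TTR and adherence come from records that exist anyway, but non-attenders would have to be contacted for the knowledge test at T1 and T5. The estimated effect may be smaller than one based on attenders alone.
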